### The Living Life to the Full classes

The Living Life to the Full (LLTTF) classes contain eight life skills sessions that teach a range of CBT-based life skills in a classroom setting based in a locally accessible location such as a library or hotel. Classes are attended by up to 16 people and last 90 minutes. Each weekly class focuses on a different common problem faced by people when they feel low or anxious. The class content is: *1) Why do I feel so bad? 2) I can’t be bothered doing anything. 3) Why does everything always go wrong? 4) I’m not good enough (low confidence). 5) How to fix almost everything. 6) The things you do that mess you up. 7) Are you strong enough to keep your temper? 8) Ten things you can do to help you feel happier straight away.* The classes use everyday terms and avoid professional terminology. They are designed to encourage an individualized plan to be made at the end of each session using a Plan, Do, Review structure [19]. Each class consists of slides, course leader notes/scripts, worksheets and a linked booklet that summarizes the topic and includes work tasks to facilitate practice at home. The classes offer guided CBT for depression delivered over a series of eight class-based sessions delivered over eight weeks. Each class is delivered using a mix of didactic teaching, question and answer discussion and tasks in groups or pairs. There are currently no equivalent classes using the same model of delivery. This accessibility is reinforced by the language used (that is, the “class” not “group”, “life skills training” instead of “CBT” and “low mood and stress” rather than “depression and anxiety”). The way of communicating CBT is highly accessible [20] and effective [21,22]. The language used in the classes includes everyday terms to describe symptoms such as stress, distress and low mood rather than the more formal diagnostic terms depressive disorder, depression and anxiety, and so on. The aim is to be inclusive and appealing to participants who are being recruited through a community-based initiative.

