A ninth session, Planning for the Future and Reunion, is held 6 weeks after the final class. The class takes place about 6 weeks after the core 8-week course as it is thought that this is an appropriate duration for participants to integrate/apply the skills they have learned in the course in their everyday lives. The revision class therefore serves as a booster session to keep participants on track with the intervention, as they are advised to continue using the resources after the group support ends for optimal benefit.

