#### Delayed access control group

Participants randomly allocated to the DAC group will be informed that they will begin attendance at the classes after a delay of 6 months. All participants will continue with any usual treatment as required. Use of anti-depressant medication and any new or ongoing mental health support will be recorded at follow-up using the CSRI.

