#### Statistical power and sample size

The primary analysis will compare changes in PHQ9 scores at 6 months between intervention groups in all participants. We have powered the study, however, to be able to detect a between-group difference of 5.5 points on the PHQ9 score within the more severe subgroup of participants scoring 10 points or more on the PHQ9 at baseline. A difference of 5.5 points is used to reflect a category change on the PHQ9 and is clinically significant as well as statistically significant. Preliminary pilot RCT data, from a mixture of intervention and control group participants, showed that for those with a PHQ9 score of 10 or more at baseline, mean PHQ9 scores reduced from 17.7 to 10.8 points after the intervention, with a standard deviation of the changes of 6.1 points.

Based on a two-sample *t*-test, a sample size of 27 participants per arm would be required to have 90% power. In the pilot, follow-up data at the primary endpoint were available for approximately 65% of those randomized. To allow for this, 84 people (two groups of 42) with PHQ9 scores of 10 or more would need to be randomized. In the pilot, one-third of participants had PHQ9 scores less than 10 points at baseline, so that 126 participants in total (two groups of 63) will be randomized in this trial. We will ensure that the required number of participants scoring 10+ on the PHQ9 have entered the study before ending recruitment.

Our pilot study strongly supports our potential to recruit 126 participants using our multi-point recruitment strategy. We have not accounted for any clustering effects in these calculations, since clustering can only occur within the intervention group (control participants will not meet in a group setting during the first 6 months of the study), and the estimate of variation in the primary outcome used in the above calculation is conservative in that it includes a component due to clustering within intervention groups. As part of the analysis we will, however, assess the extent to which the study findings are sensitive to any clustering effects.

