#### Statistical analyses

The primary analysis will use analysis of covariance, testing the difference between groups in PHQ9 and GAD7 scores in all participants at 6 months with adjustment for baseline values. This is more efficient than two-sample *t*-tests, increasing the power of the study. An intention-to-treat approach to analysis will be used.

A criticism sometimes made of research studies that allow self-referral and utilize community-based recruitment is that patients are not significantly depressed. Planned secondary analyses will therefore be carried out for those with PHQ9 scores of 10 or more (that is, moderately severe depression), and for those with scores less than 10, at baseline. We will test whether the intervention effect interacts with baseline PHQ9 score (in other words, is the intervention more or less effective dependent upon the baseline PHQ9 score). The model for all participants will also be extended to assess the impact of baseline participant characteristics including age, gender, antidepressant use, level of depression and measures of compliance with the intervention (and, for those factors that influence outcome, their interaction with intervention). Similarly, regression methods, chosen according to the distribution of outcome variable being investigated, will be used for other outcomes. Simple and multiple imputation methods will be explored for the primary outcome to assess the sensitivity of the main study findings to alternative assumptions regarding missing data.

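### The secondary extended model treats class compliance as a baseline characteristic, but it arises after randomisation and does not exist in the delayed arm, so its interaction with treatment cannot be estimated

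*Protocol article*

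**What the plan says.** The Statistical analyses section of the protocol article sets out two models that matter here.

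- **Primary model.** An analysis of covariance compares the arms "in PHQ9 and GAD7 scores in all participants at 6 months with adjustment for baseline values". The section adds: "An intention-to-treat approach to analysis will be used". Compliance is not in this model.
- **Extended model.** "The model for all participants will also be extended to assess the impact of baseline participant characteristics including age", and the list goes on: "gender, antidepressant use, level of depression and measures of compliance with the intervention (and, for those factors that influence outcome, their interaction with intervention".

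Three other sections fix what compliance can mean at 6 months.

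- **The classes.** The course is "delivered over a series of eight class-based sessions delivered over eight weeks". In addition, "A ninth session, Planning for the Future and Reunion, is held 6 weeks after the final class". All nine sessions fall after randomisation.
- **The delayed arm.** DAC participants "will be informed that they will begin attendance at the classes after a delay of 6 months".
- **Sample size section.** It confirms that "control participants will not meet in a group setting during the first 6 months of the study".

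The article names no separate method for compliance.

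**The concern.** A covariate in a treatment model should be fixed before randomisation, so that it cannot carry any consequence of allocation. Attendance fails that test. It is also defined in only one arm at the time of the outcome, so a model of both arms has nothing with which to separate the effect of compliance from its interaction with treatment.

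An analyst who follows the text meets a singular model and will probably drop the interaction. The fit then runs, but its treatment coefficient no longer estimates the effect of being offered the classes. Its compliance slope is confounded by whatever makes some people attend and others not. An apparent dose-response, together with a treatment coefficient pointing towards harm, can then appear when the classes do nothing.

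**Working it through.** The plan attaches no figure to this analysis, so there is none to reproduce for it. Its sample size is not in dispute and does reproduce. A difference of 5.5 with SD 6.1 gives power 0.902 at 27 per arm by the t-test (two-sided 5% assumed, as the article states no level). Then 27/0.65 = 41.5, so 42 per arm and 84 in all, and 84/(2/3) = 126.

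**Step 1: estimability (no assumptions needed).** Let T = 1 for immediate access (IA) and 0 for DAC, and let A be compliance. By design A = 0 or undefined whenever T = 0.

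- *DAC coded 0.* A × T = A in IA because T = 1, and A × T = 0 = A in DAC. The two columns are identical. The matrix with columns intercept, T, baseline, A and A × T had rank 4 of 5 in every simulated data set.
- *DAC coded missing.* A complete-case fit drops every control, so T is constant and no treatment contrast remains.

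**Step 2: meaning of the coefficients if only the main effect of A is kept (DAC = 0).** Leave out other covariates for clarity. The fitted DAC value is the DAC mean, and the IA line passes through the IA means. Therefore

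coefficient of T = (difference in arm means) − (slope of A) × (mean A in IA).

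This is the fitted difference at zero attendance. It equals the intention-to-treat difference only when the slope is zero.

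**Step 3: size with no true effect.** Inputs:

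- 41 per arm: 63 × 0.65 = 40.95, from the article's group size and pilot follow-up rate.
- Outcome SD 6.1: the article's SD of changes among pilot participants with PHQ9 of 10 or more, applied here to everyone.
- Attendance mean 5 of 8 sessions, SD about 2.5 before limiting to 0–8: assumed.
- Correlation r between attendance and better prognosis: assumed, with a range shown. It must be read as the residual correlation after the baseline covariates, because the simulated model contains only arm and sessions.

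| r | Treatment coefficient (PHQ9 points) | Slope per session | Trials with p < 0.05: slope |
|---|---|---|---|
| 0 | about 0 | about 0 | about 5% |
| 0.1 | +1.3 | −0.26 | 9% |
| 0.2 | +2.6 | −0.54 | 22% |
| 0.3 | +3.9 | −0.80 | 45% |

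At r = 0.3 the treatment coefficient itself is significant in about 33% of null trials. The unadjusted contrast stays at about 0 throughout.

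The rows agree with Step 2. At r = 0.3 the implied mean attendance is 3.9/0.80 = 4.9 sessions, and 0.26 × 4.9 = 1.3 and 0.54 × 4.9 = 2.6. The slope is also of the expected order: r × 6.1/2.5 = 0.73 at r = 0.3, a little below the simulated 0.80 because limiting to 0–8 narrows the spread of attendance.

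**Step 4: with a true effect.** If the effect is −5.5 whatever the attendance, then at r = 0.3 the coefficient becomes −5.5 + 3.9 = −1.6. A second simulation used 126 participants, baseline adjustment and a benefit proportional to attendance, with a true intention-to-treat effect of −5.5. The ANCOVA without compliance recovered −5.5. The compliance-adjusted coefficient was 0.0, +2.0 and +4.0 when an unmeasured prognostic factor that also drives attendance was worth 0, 1 and 2 points per SD. Even without confounding, then, the coefficient is not the intention-to-treat effect. Its SD was also about twice as large (2.1 against 1.05).

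**The case against.** **The trial's treatment effect is not at risk.** This stands. The primary ANCOVA adjusts for baseline values only. A reader might infer that the trial's main result would be biased. The documents do not support that, because compliance enters only an additional model, and none of the listed research questions asks about attendance.

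**The size of the bias is assumed.** This stands too. The documents give no link between attendance and prognosis, and adjustment for baseline severity would absorb part of any such link. At r = 0 there is no spurious effect in a null trial. The rank deficiency in Step 1 depends on none of this.

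**The definition and coding of compliance belong in an analysis plan that is not shown.** This stands only in part. The definition may well be there, but no coding of DAC rescues the stated interaction. The defect lies in what the article specifies, not in what it omits. Reading compliance as listed beside the baseline factors, rather than as one of them, does not help either, since it still enters a model of all participants. The Economic analysis section's own list of baseline characteristics (PHQ9 score, age, gender, antidepressant use) does not include it.

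**Testing interactions only for factors that influence outcome.** A reader might call this a second error. It is largely a matter of preference here, because the same section plans the interaction with baseline PHQ9 score without that condition.

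**Misreporting.** A reader might also infer that the result would be presented as evidence on how many sessions are needed. Nothing in the article says so.

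**Conclusion.** The point holds for the secondary extended model only. As written, the compliance-by-intervention interaction cannot be estimated under either coding of DAC; that follows from the design alone. If the model is reduced to a compliance main effect, its treatment coefficient is the effect at zero attendance and its slope is a comparison of self-selected groups. For a null trial the spurious treatment coefficient runs from about 0 to +3.9 PHQ9 points over assumed residual correlations of 0 to 0.3, and the false-positive rate for the slope from about 5% to 45%. Those sizes rest on the assumed attendance distribution and correlation and on SD 6.1 applying to all participants. This calls for a correction to a secondary analysis. It does not threaten the primary result or the sample size.

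**What to change.** Remove compliance and its interaction with intervention from the covariate list of the all-participant model, leaving age, gender, antidepressant use and level of depression at baseline. Assess compliance separately and label it exploratory, in one of two ways:

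- **Complier average causal effect**, with randomisation as the instrument and sessions attended as the exposure. As DAC attend no sessions before 6 months, the unadjusted per-session estimate is the intention-to-treat difference divided by mean IA attendance. State the exclusion restriction (allocation affects outcome only through attendance) and expect a wider interval than from the naive fit. If a threshold of attendance is used as the exposure, state that this further assumes no benefit from attendance below it.
- **Description within IA only**, with no causal claim.

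The cost is a change of wording. Sample size and visits are unchanged. Table 1 lists no attendance measure, so the plan should confirm that attendance is recorded for each session, as its intention to use compliance measures implies.

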#### Economic analysis

The CSRI and EQ5D will be used to measure use of services and current state of health; these will be used in the health economic analysis of the intervention. Economic analysis will take a health service perspective as recommended by NICE. We shall apply generalized linear models for costs and health utilities, with bootstrapping and the method of recycled predictions to estimate the mean and uncertainty in the Incremental Cost Effectiveness Ratio [36]. Interpretation will be aided using cost-effectiveness acceptability curves derived using the net-benefit approach with values between £0 and £100,000 placed on a quality-adjusted life year gain so as to include the threshold used by NICE.

We shall assess the cost-effectiveness of the LLTTF classes in relation to baseline participant characteristics, including PHQ9 score, age, gender and antidepressant use. We shall assess the sensitivity of our findings to variations in the cost of delivering the intervention.

## Discussion

### Importance of the project

If this RCT demonstrates that the intervention is effective and cost effective then this has important implications for healthcare delivery. We hope that the community recruitment and AOD support will include people into the project who might otherwise fail to engage in traditional NHS-based services thus addressing the wider treatment gap. The design allows a detailed description of those recruited in order to understand the current treatment, severity, chronicity, diagnostic category and impact of those recruited.

As well as testing the effectiveness and cost-effectiveness of the intervention, the design also tests the attractiveness of partnership delivery through the voluntary sector - an area where outcome data are often poorly available.

### Benefits to participants

Participation within this research will allow adults who are experiencing symptoms of low mood/depression to take part in CBT-based educational classes aimed at addressing these issues. Previous research has provided empirical evidence that CBT is effective in aiding a variety of problems related to depression and anxiety. The results from the current research will be used to indicate whether the classes are an acceptable and effective intervention for low mood and stress in self-referring participants. By assessing the acceptance and feasibility of the package for this population, we will be able to gain a key insight into how similar interventions can be best delivered to adults within the community.

Participant safety and wellbeing is paramount in the study; therefore, in the participant information sheet, participants will be made aware of the fact that they should exercise normal caution in relation to their interactions with other individuals attending the classes, especially with regard to meeting outside the classes or sharing telephone numbers, email addresses and other personal information or contact details. Participants will also be told that they can seek the advice of the life skills trainer and/or the research team for advice if any problems do arise.

### Collaboration with action on depression – public engagement and knowledge exchange

AOD, the charity delivering the classes, are experienced in working with the proposed population and their facilitators will be able to assist any individuals who may need additional help during the study by giving them information about how to access alternative forms of support and the appropriate action to be taken if the participants feel their condition is deteriorating.

The self-referral, community-based approach adopted in the study may help access hard to reach individuals including young men, black and minority ethnic groups and elderly adults. However, it is acknowledged that additional consideration may be needed in the recruitment of these individuals. It would be useful for future research in this area to specifically consider minority groups both in terms of recruitment methods and also adaptation of interventions to ensure they are relevant.

#### Dissemination

Dissemination will include an executive summary, open access journal publications and conference presentations. The main journal publication will present the findings in relation to the primary and secondary research questions of the study, with a secondary health economic paper. Newsletters will be sent to all participants summarizing the study outcomes. We will also disseminate findings via the newsletters on the widely used http://www.livinglifetothefull.com website which has over 200,000 signed up members including over 9000 practitioners. AOD will also disseminate results to those receiving their newsletters and via their website. Therefore, both the professional community and individuals with depression will be made aware of the study and its findings.

#### Trial status

The project commenced in July 2012. Ethical approval has been gained and the first round of recruitment has been completed and 104 participants randomized. Four IA courses, two in Edinburgh and two in Glasgow have been delivered. The DAC participants will complete their courses in April 2013. A second recruitment phase is taking place with the aim of recruiting sufficient participants to achieve the required numbers defined by the power calculation. The expected completion date of the RCT is January 2014.

## Abbreviations

AOD: Action on Depression; cCBT: Computerized cognitive behavioral therapy; CBT: Cognitive behavioral therapy; CSQ-8: Client satisfaction questionnaire-8; CSRI: Client Service Receipt Inventory; DAC: Delayed access control; EQ5D: ; GAD7: Generalized anxiety disorder 7; HADS: Hospital Anxiety and Depression scale; HI: High intensity; IA: Immediate access; LI: Low intensity; LLTTF: Living Life to the Full; MINI: Mini International Neuropsychiatric Interview; NHS: National Health Service; NICE: National Institute for Health and Clinical Excellence; PHQ9: Patient health questionnaire-9; RCT: Randomized controlled trial; WSAS: Work and Social Adjustment Scale.
